## Abstract

Selective mutism (SM) is a relatively rare anxiety disorder, characterized by a child's consistent failure to speak in various specific social situations (e.g., at school), while being able to speak in other situations (e.g., at home). Prevalence rates vary from 0.2% to 1.9%. SM is usually identified between the ages of 3–5 years. It is often underdiagnosed and consequently children receive no or inadequate treatment, with negative consequences for school and social functioning. If left untreated, SM can result in complex, chronic anxiety and/or mood disorders in adolescence and impaired working careers in adulthood. Currently, no evidence-based treatment for SM is available in the Netherlands, therefore this study aims to [1] test the effectiveness of a treatment protocol for SM that is carried out at school, and to [2] identify baseline predictors for treatment success.

This article presents the design of a randomized controlled trial into the effectiveness of a behavioral therapeutic protocol for selective mutism in children (age 3–18). The expected study population is n = 76. Results of the treatment group (n = 38) will be compared with those of a waiting list control group (WCG) (n = 38). Pre and post treatment assessments will be conducted at comparable moments in both groups, with baseline assessment at intake, the second assessment at 12 weeks and post-assessment at the end of treatment. If proven effective, we aim to structurally implement this protocol as evidence-based treatment for SM.

## Background

1

Selective mutism (SM) is a severely debilitating anxiety disorder, mostly occurring in young children [1]. It is characterized by consistent failure to speak in situations where speaking is expected (e.g., in school), while speaking freely in other situations (e.g., at home). Prevalence rates vary between 0.2% and 1.9% [2,3], with a boys:girls ratio of 1:2 [3]. SM is more common in bilingual or multilingual children [4]. Not speaking in social situations impairs personal, social, and academic development. If left untreated, SM can have a chronic character [5,6].

Currently, it is still unclear which mechanisms affect treatment success in children with SM. For childhood anxiety disorders in general, it is known that parental factors (parenting style, parental psychopathology and previous health care consumption) can influence treatment success [7]. A study of Oerbeck, Stein [8] shows that children who are treated for SM at a younger age, show faster treatment progress than older children. These results were maintained on longer term [9]. In another study of Oerbeck, Overgaard [10], besides age, higher severity at baseline, familial anxiety and compliance of parents were predictors of treatment success. Also the predictive value of bilingualism, gender, comorbidity and minority status was investigated. These results were less compelling. As the authors also note, possibly due to a relative small sample size (N = 32) effect sizes were small. Especially at follow-up due to consequences of drop-out during the study. In our clinical institution we see a large, heterogeneous population of children with SM, with many bilingual children, as also described by Elizur and Perednik [4] and Toppelberg, Tabors [11]. Although several evidence-based treatments, based on (cognitive) behavioral therapy are available for anxiety disorders in children [12], studies investigating treatment effects in children with SM are still limited. A recent non-randomized trial showed that behavioral techniques with additional parent child interaction therapy improve SM symptoms [13]. Three previous randomized controlled trials (RCT) investigated showed that behavioral therapy was effective for selective mutism [8,14,15]. These studies provided therapy in different settings i.e. in the clinical setting [14,15] and at home before starting at school [8]. Unfortunately sample sizes in these studies are relatively small (N = 21, N = 24, N = 29). Currently, no evidence-based protocol specifically for the treatment of SM is available for the Dutch population. Since such a protocol is urgently needed in clinical practice, in our institution the protocol ‘Speaking in school, a matter of doing’ was developed [16]. A considerable strength compared to most previous studies is that this treatment is provided at school, where the problem is most present. The rationale is that treatment in school makes it easier to generalize speaking behavior to settings where the child still has difficulty speaking. In this RCT we aim to investigate the effectiveness of this behavioral therapeutic protocol, compared to a waiting list control group. A major methodological advantage is that we aim to execute a sufficiently powered RCT. Secondly, we aim to identify putative predictors for treatment success in children with SM.

## Methods/design

2

***Design:*** this study is a single-center, single-blinded randomized controlled trial (RCT), comparing protocolized behavioral therapy for selective mutism to a waiting list control group.

***Inclusion:*** eligible are children between the age of 3–18 years old, with an estimated IQ of 85 or higher, who understand Dutch and are referred to our academic center for diagnosis and treatment of selective mutism between September 2018 and March 2020. This large age span covers all consecutive patients referred to our institution. Though the vast majority of these children is under the age of 8, we also get referrals up to 18 years.

***Exclusio******n******:*** ineligible are children who have primary diagnoses other than selective mutism. Comorbidity is not excluded, but the primary and most impairing diagnosis has to be selective mutism. During the intake, it will be assessed what the most urgent need for help is and what type of care is most indicated. In the case that treatment is indicated for a comorbid diagnosis at first, the child will be excluded from the study.

### Patient recruitment and procedure

2.1

Parents of eligible patients will be personally informed about the research project by the psychologist-researcher and will receive written information about the research project. Written informed consent will be obtained from parents/guardians for patients under the age of 12. From the age of 12 written consent will also be obtained from them. Only patients (≥12 years), who have given informed consent, or whose parents have signed informed consent will participate in this study.

After informed consent is provided, children are randomly assigned to treatment for selective mutism (N = 38) or the waiting list control group (WCG: N = 38).

Randomization will be stratified for gender, age (children aged until 7 years old are stratified into the “young” group, and children ages 8 and up are in the “old” group) and bilingualism (speaking one language, i.e. Dutch, versus speaking multiple languages). Randomization will be performed by an independent researcher, who will inform the therapists regarding the randomization outcome.

### Intervention

2.2

A standardized, behavioral therapeutic protocol was developed in the Netherlands to treat SM [16]. Children learn in different steps, by using gradual exposure to challenging situations, shaping and modelling. The advantage and innovative aspect of this protocol is that treatment is carried out solely at school. Since at school the problem is present most evidently, a therapist goes to school to practice individually with the child. This helps to generalize the learned exercises to the school situation. Every week the child learns step by step to make sounds and to speak, after which the speaking behavior is extended to various places in school with as the final goal: participating actively in the circle discussion in the classroom.

The protocol is mainly based on behavioral techniques, with as the primary aim stepwise practicing to speak. However, for children from 12 years and older, additional cognitive elements (e.g. helping thoughts) which are used in traditional cognitive behavioral therapy for anxiety [17], are available to be used optionally. The therapist involves the teacher as a co-therapist in the treatment process. After each weekly treatment session at school, the therapist instructs the teacher how profit can be maintained and which exercises to practice during the week. The teacher then continues the exercises throughout the week, finding short moments in time during the week to practice with the child. The therapist is in touch with the teacher face to face after each therapy session, by email or phone when necessary.

Previous clinical experience learns that the average treatment duration with this protocol is 22 weeks.

### Assessments

2.3

Parents, children older than 8 years and teachers will complete questionnaires online. Parents will also be interviewed by the researcher.

The psychologist-researcher who performs the assessments will be blinded for participants’ allocated intervention. Children and parents, as well as the treatment-staff are explicitly asked not to talk about their randomization condition with the psychologist-researcher. Both groups are treated with the standard treatment protocol for selective mutism.

Assessments will be carried out at the following time points [1]: T1, baseline assessment during intake, before intervention starts [2]; T2, 12 weeks after baseline, either after first 12 weeks of treatment or 12 weeks of waiting list period [3]; T3, after last treatment session. If at any of the assessments or during the waiting list and/or treatment period there is sudden need for immediate intervention (e.g. in the event of a crisis), unblinding will take place to ensure that the participating patient receives the necessary care.

To acquire information from all informants (parents, guardians, teachers, children/adolescents), standardized questionnaires and interviews will be used with adequate psychometric properties, except for the Dutch translation of the SMQ, which will be validated in this study.

In Table 1, all assessments are listed.

**Table 1 tbl1:** Measures per assessment moment.

Instrument	Variable	Assessment moment		
		T1	T2	T3
Primary outcomes				
Selective Mutism Questionnaire (SMQ)	Selective mutism symptoms	P	P	P
Selective Mutism section of Anxiety Disorders Interview Schedule (ADIS-C)	Selective mutism symptoms	P	P	P
Secondary outcomes				
ADIS-C	Anxiety and mood symptoms	P	a	P
Child Behavior Checklist (CBCL)	Behavioral and emotional problems	P	P	P
Teacher Report Form (TRF)	Behavioral and emotional problems	T	T	T
Youth Self Report (YSR)	Behavioral and emotional problems	C	C	C
Self-Perception Profile Child/Adolescent (SPP–C/A)	Self-image	C		C
Child Health Questionnaire (CHQ)	Quality of life	P		P
Predictors				
Adult Self Report (ASR)	Behavioral and emotional problems	P		
EMBU-P	Parenting style	P		
Demographic variables	Demographics	P		
Health care consumption questionnaire	Health care consumption	P		

P: Parents.

T: Teacher.

C: Child.

SMQ: Selective mutism questionnaire.

ADIS-C: Anxiety Disorder Interview Schedule – Children's version.

CBCL: Child Behavior Checklist.

TRF: Teacher Report Form.

YSR: Youth Self Report.

SPP-C/A: Self-Perception Profile Child/Adolescent.

CHQ: Child Health Questionnaire.

ASR: Adult Self Report.

EMBU-P: Egna Minnen Beträffande Uppfostran – Parent version.

a At T2, only the reported sections of the ADIS-C interview at T1 are assessed.

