*Sample size calculation*

A preliminary randomized clinical trial into behavioral treatment of selective mutism showed an effect size of Cohen's d = 0.58 on speaking in social situations [15]. To determine effects on our primary outcome (i.e. the pre versus post treatment change (T1-T3) on selective mutism symptoms), based on an effect size of d = 0.58 (medium effect size), an alpha of 0.05 (two-tailed) and a power of 0.8, a sample size of 76 (38 per group) is needed [30].

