### Possible difference between participants and drop-outs

3.1

Clinical experience in this patient population shows us that drop-out during treatment is rare. To be able to compensate for possible drop-out during the study (if needed), we aim to include 100 participants as a safety measure. A drop-out analysis on the drop-out population will be conducted: it will be studied whether there are possible differences in variables (such as: gender, age, socio-economic status, bilingualism, severity of selective mutism at baseline assessment and parental psychopathology) between the population that participates until the end of their treatment and the population that drops out. In this way it can be checked whether there is a selective dropout. A selective dropout can lead to selection bias, which could be statistically adjusted for.

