### Intention to treat

3.2

The statistical analyses will be based on the intention-to-treat principle. If appropriate, secondary analyses will be conducted using a per-protocol basis.

Primary and secondary outcomes: Pre-post changes (pretreatment and post treatment assessment of the treatment versus WCG group) on the primary outcome (symptoms of selective mutism) will be tested with repeated measures analyses (factorial repeated measures ANOVA). To determine pre-post change in treatment outcome (responders vs. non-responders) paired sample t-tests will be executed. The effectiveness on secondary outcome measures: symptoms of anxiety/depression, self-image, quality of life and care consumption, will be tested with the same analyses. With linear and logistic regression predictors (e.g., gender, age, socio-economic status, bilingualism, parental psychopathology and parenting styles) for treatment outcome can be determined (p < .05). In the analyses, the number of treatment sessions will be included as a covariate.

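### T3 is defined only by the last treatment session, with no rule for children who stop early or never start, so the T1–T3 intention-to-treat analysis tends towards a completers' analysis

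*Protocol article*

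**What the plan says.** All references are to the protocol article.

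- **Primary window.** The sample size paragraph in section 2.5 names the primary outcome as "the pre versus post treatment change (T1-T3) on selective mutism symptoms".
- **T3.** Section 2.3 gives "T3, after last treatment session". The abstract agrees, with "the second assessment at 12 weeks and post-assessment at the end of treatment". Neither gives a calendar time.
- **Treatment length.** Section 2.2 reports from clinical experience that "the average treatment duration with this protocol is 22 weeks". No fixed length or maximum is stated.
- **T2.** This visit has a date: "T2, 12 weeks after baseline, either after first 12 weeks of treatment or 12 weeks of waiting list period". Table 1 lists both primary instruments (the SMQ and the selective mutism section of the ADIS-C) at T1, T2 and T3.
- **Treatment in both arms.** Section 2.3 says "Both groups are treated with the standard treatment protocol for selective mutism", so T3 in the waiting-list arm also follows treatment.
- **Drop-out.** Section 3.1 calls drop-out rare, aims for 100 inclusions against the 76 needed, and plans a comparison "between the population that participates until the end of their treatment and the population that drops out". It adds that selective drop-out could be adjusted for.
- **Analysis.** Section 3.2 says "The statistical analyses will be based on the intention-to-treat principle", names a factorial repeated measures ANOVA for the primary outcome, and allows per-protocol analyses as secondary.

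**The concern.** T3 closes the primary window, and it is the only post-baseline visit triggered by treatment received instead of time since entry. Whether a child has a T3 value, and when it is taken, therefore depends on events after randomisation. Intention to treat is meant to remove that dependence.

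Section 3.1 has two groups, completers and drop-outs. A child who stops treatment but would still answer questionnaires fits neither clearly.

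Two things are at stake. First, children for whom treatment failed, or who left the waiting list, may disappear from the main comparison for reasons that differ by arm; the intention-to-treat and per-protocol results would then rest on much the same children. Second, the predictor analysis of treatment success may lose some of its clearest failures.

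**Working it through.** The point rests on how stated rules fit together, so the main check is to apply them to each kind of child.

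**1. The visit rules applied**

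| Child | T2 (12 weeks from baseline) | T3 (tied to last session) |
|---|---|---|
| Completes treatment | Scheduled | Defined; date varies with treatment length |
| Stops early, either arm | Scheduled if still followed | Unscheduled time, or none if counted as a drop-out |
| Never starts, either arm | Scheduled if still followed | Not defined: there is no last session |

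Never starting is possible in both arms. Randomisation follows consent (section 2.1) and T1 precedes the intervention (section 2.3), so a treatment-arm child can also leave before the first session. The 12-week wait gives waiting-list children more time to do so.

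**2. The analysis applied**

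A factorial repeated measures ANOVA in its usual form uses only children with a value at every time point in the model. Children in the last row of the table, and those in the middle row without a T3, fall out of the T1–T3 analysis.

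**3. Direction of the bias**

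For each arm let q be the fraction without T3, and D the mean improvement of children with T3 minus the mean improvement of those without. The mean of all children is (1 − q) × (mean with T3) + q × (mean without T3), so the mean with T3 exceeds the mean of all children by q × D. The bias in the difference, treatment minus waiting list, is

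q_T × D_T − q_W × D_W.

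The article gives neither q nor D. Taking q = 10% and D of size 0.5 SD purely as assumptions, each term has size 0.10 × 0.5 = 0.05 SD:

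- loss only in the treatment arm, failures missing: +0.05
- equal loss of failures in both arms: 0.05 − 0.05 = 0
- loss only in the waiting-list arm, failures missing: −0.05
- failures missing from treatment, improvers missing from the waiting list: 0.05 − (−0.05) = +0.10

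The sign changes with the assumption, so the documents fix neither direction nor size.

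**4. Precision**

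The plan's own figure first: d = 0.58, two-tailed alpha 0.05 and power 0.80 are said to need 38 per group. A two-sided t-test needs 47.6, so 48, and 38 per group gives power 0.70. That mismatch is a separate matter, noted here only so that the next figures can be read.

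The recruitment margin is 1 − 76/100 = 24%. With 100 recruited (50 per arm), an assumed share without T3 and only complete cases analysed:

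| Share without T3 | n per arm | Power at d = 0.58 |
|---|---|---|
| 0% | 50 | 0.82 |
| 10% | 50 × 0.90 = 45 | 0.78 |
| 20% | 50 × 0.80 = 40 | 0.73 |
| 24% | 50 × 0.76 = 38 | 0.70 |

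Extra recruitment replaces lost numbers, but it does not restore the lost children.

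**The case against.** The strongest reply has four parts.

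*T2 already supplies an intention-to-treat comparison.* This stands. T2 is dated from baseline in both arms and carries both primary instruments. A reader might infer that intention to treat cannot be carried out at all; the article does not support that. T2 does not settle the point, though, because the stated primary window ends at T3.

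*The article never says that children who stop are no longer assessed.* This also stands. Section 3.1 describes a bias check and speaks of drop-out both during treatment and during the study. Nor does section 2.3 give an interval between last session and T3, so it is a possible reading, not a stated rule, that an early stopper's T3 would come before T2.

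*Follow-up and missing-data details belong in the full protocol or analysis plan.* This stands in part. A mixed model or imputation may well be specified there. But the visit rule is stated in this article, and no analysis method can recover a value that the rule never caused to be collected.

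*Moving T3 to one fixed date for everyone would change the question.* This stands and limits the fix. With treatment averaging 22 weeks, and assuming that it starts at baseline in one arm and straight after the wait in the other, T3 falls at about 22 weeks and about 12 + 22 = 34 weeks. A single date would catch many waiting-list children in mid-treatment and replace an end-of-treatment outcome with another. Complete T3 data would also leave untouched the separate fact that both arms have been treated by then.

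**Conclusion.** The concern holds as a poorly defined endpoint for two groups of children, not as an analysis that is impossible. As written, never-starters have no T3, early stoppers have an unscheduled T3 or none, and the named ANOVA ordinarily excludes whoever lacks it.

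A reader might infer that never starting is confined to the waiting list; it is only more likely there. A reader might also take the 24% recruitment margin as an expected loss and express the resulting bias as a share of the planned effect of 0.58. The article does not support that: it calls drop-out rare and the margin a safety measure, a bias in one arm's mean is not a bias in the difference between arms, and waiting-list children who leave because they improved would reverse the sign of that arm's term.

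The conclusion rests on two assumptions: that the ANOVA is run in its usual complete-case form, and that no fuller document already separates stopping treatment from leaving the study. If drop-out is as rare as stated, the effect is small, and so is the cost of repair.

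**What to change.** Amend sections 2.3, 3.1 and 3.2 as follows.

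1. State that stopping treatment, or never starting it, does not end follow-up.
2. Collect T2 at 12 weeks in every randomised child for whom consent has not been withdrawn.
3. Keep T3 at the end of treatment for children who complete it. For those who stop early or never start, take T3 at a default date counted from T1 or randomisation and set in advance for each arm.
4. Analyse all available values in the allocated arm, with a method that does not discard children lacking one visit.
5. Record stopped or never started treatment as a status separate from left the study, and run the section 3.1 drop-out comparison on the latter.

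The cost is protocol wording plus the existing online questionnaires and a parent interview for a few families no longer in treatment. No new patients or instruments are needed. The small downside is the burden of contacting those families.

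### With T1 as the pre-treatment value in both arms, the waiting-list children's T1-T3 change includes 12 untreated weeks, so within-child pre-post and pooled predictor analyses mix waiting with treatment

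*Protocol article*

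**What the plan says.** Section 2.3 (Assessments) sets three time points:

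- T1 is the same in both arms: "T1, baseline assessment during intake, before intervention starts".
- T2 is 12 weeks later, "either after first 12 weeks of treatment or 12 weeks of waiting list period".
- T3 has no calendar week: "T3, after last treatment session".

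The same section states: "Both groups are treated with the standard treatment protocol for selective mutism". The waiting-list arm has therefore also been treated by T3.

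The sample size paragraph defines the primary outcome as pre versus post change on selective mutism symptoms and labels it T1-T3, with no separate starting point for the waiting-list arm. Section 3.2 refers to pre-treatment and post-treatment assessments without tying them to time points. It plans repeated measures ANOVA, paired t-tests for pre-post change and regression for predictors ("With linear and logistic regression predictors"), and it enters the number of treatment sessions as a covariate. It assigns no analysis to T2.

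Section 2.2 (Intervention) gives the treatment length only as past experience: "the average treatment duration with this protocol is 22 weeks". The abstract says: "Pre and post treatment assessments will be conducted at comparable moments in both groups".

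**The concern.** T1 is the start of treatment in one arm and the start of waiting in the other. If T1 is the pre-treatment value for every child, a waiting-list child's T1-T3 change is the sum of whatever happened in 12 untreated weeks and whatever happened under treatment. A paired test on that difference, or a regression that pools both arms, reads the whole sum as treatment change. Identifying predictors of treatment success is one of the trial's two stated aims, so this matters beyond the paired tests.

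A second issue follows from T3 falling at the last session. Treatment length may depend on how quickly a child responds. The number of sessions is then partly a result of response, and adjusting for it can remove part of a predictor's association with outcome. The background cites evidence that children treated younger "show faster treatment progress than older children", which is the kind of effect that could be absorbed.

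That the randomised T1-T3 contrast compares two treated groups is a separate matter and is not developed here.

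**Working it through.** The plan gives no figure of its own for this point, so the check is interval arithmetic on its stated times, followed by a range for the size.

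**Inputs from the document.** Waiting period 12 weeks (section 2.3). Average treatment duration 22 weeks (section 2.2). Planned arms equal, 38 each (sample size paragraph).

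**Assumptions, not in the document.** Waiting-list treatment starts right after T2. Improvement while waiting is w = 0 to 0.3 SD. Improvement under treatment is D = 0.8 SD, the same in both arms.

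**Step 1: length of the T1-T3 interval**

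- Treated arm: about 22 weeks.
- Waiting-list arm: 12 + 22 = 34 weeks.
- Untreated share in the waiting-list arm: 12/34 = 35%.
- For assumed treatment lengths of 12 and 36 weeks the share is 12/24 = 50% and 12/48 = 25%.

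**Step 2: overstatement of treatment change**

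The waiting-list T1-T3 change is D + w, so it overstates D by w/D. Pooled over equal arms, the mean change is D + w/2, an overstatement of w/(2D). With D = 0.8:

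| w (SD) | Waiting-list change | Overstatement | Pooled change | Overstatement |
|---|---|---|---|---|
| 0 | 0.80 | 0% | 0.80 | 0% |
| 0.1 | 0.90 | 12.5% | 0.85 | 6% |
| 0.2 | 1.00 | 25% | 0.90 | 12.5% |
| 0.3 | 1.10 | 37.5% | 0.95 | 19% |

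The result depends on D. At w = 0.3, D = 0.58 gives 0.3/0.58 = 52% in the waiting-list arm and 26% pooled; D = 1.0 gives 30% and 15%. If children worsen while waiting, the sign reverses and treatment change is understated.

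**Step 3: does the sessions covariate correct this?** No. Two children with 22 weekly sessions have the same covariate value, yet one has a 22-week and the other a 34-week T1-T3 interval.

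**Step 4: can T2 repair it?** In Table 1 the SMQ, the ADIS-C selective mutism section, the CBCL, the TRF and the YSR are measured at T1, T2 and T3. For waiting-list children T2-T3 is then about 22 weeks, matching T1-T3 in the treated arm. Self-image (SPP) and quality of life (CHQ) are measured at T1 and T3 only. The remaining ADIS-C sections are repeated at T2 only where reported at T1.

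**Step 5: how far might the response-dependent T3 matter?** An illustrative simulation with 76 children assumed that treatment ends when a goal is reached or at a maximum length, with a median speed of one goal per 22 weeks and a predictor effect of 0.35 on log speed. Power to detect the predictor:

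| Assumed maximum length | Change at last session | Same, adjusted for sessions |
|---|---|---|
| 22 weeks | 83% | 37% |
| 30 weeks | 48% | 12% |
| 40 weeks | 18% | 5% |
| 60 weeks | 7% | 6% |

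At a fixed 12 weeks of treatment power was about 97%, again with 76 children; the treated arm alone has 38, so power there would be lower. The spread of the table shows that the answer is set by an assumption the document does not supply.

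**The case against.** **The predictor outcome is inferred.** Section 3.2 speaks only of treatment outcome, and T1-T3 is named once, in the sample size paragraph. A condensed article may leave the exact definition to a fuller document. This stands as a limit, and the predictor part is worded conditionally for that reason. T1-T3 is nevertheless the only definition of pre-post change that the article gives.

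**Randomisation protects the predictors.** Allocation is random and stratified by gender, age and bilingualism, so a waiting drift common to all children is not confounded with those factors. This also stands: a common drift adds noise but does not bias the coefficients. It does not help where the drift itself varies with a predictor. The pooled coefficient then contains about half of the predictor's association with untreated change.

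**The abstract describes stages of care.** Both arms are assessed at intake, at 12 weeks and at the end of treatment, and the article discloses this. That is fair, and the sentence is loose rather than false. For T3, however, the elapsed time differs by about 12 weeks.

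**The stronger reading.** A reader might infer that the plan hides predictors of speed of response and that the outcome should become change per week or treatment duration. The documents do not support this. They give a final goal and an average duration, but no rule for when treatment ends. If duration is unrelated to response (assumed mean 22, SD 5 weeks), a predictor correlating 0.3-0.5 with speed still correlates 0.22-0.37 with end-of-treatment change, and 0.24-0.41 after adjustment for duration, so the covariate would then help. The stated aim is treatment success, not speed. A duration outcome would also score an early-ending failure as fast.

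**Conclusion.** The point holds for the definition of the pre-treatment value. Given the stated time points and T1-T3 as pre-post change, about 12 of 34 weeks (35%) of the waiting-list interval are untreated, against none of about 22 weeks in the treated arm. This rests on waiting-list treatment starting right after T2 and lasting about the stated average. The resulting overstatement, 0-38% in the waiting-list arm and 0-19% pooled, rests on the assumed drift of 0-0.3 SD and treatment change of 0.8 SD, and is nil if nothing changes during waiting.

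The effect of a response-dependent T3 on predictor findings is a possibility, not an established defect. It justifies sensitivity analyses, not a new outcome.

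**What to change.** In section 3.2:

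1. For within-child pre-post and predictor analyses, take T2 as the pre-treatment value for waiting-list children and T1 for treated children, for the SMQ, the ADIS-C selective mutism section, the CBCL, the TRF and the YSR.
2. State that self-image and quality of life have no T2 value, so their waiting-list change includes the waiting period.
3. Describe T3 as an uncontrolled end-of-treatment measure.
4. Keep treatment success as the predictor outcome. Report the predictor models with and without the number of sessions, and add T1-T2 change in the treated arm as a fixed-time sensitivity analysis.

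In the abstract, limit the statement on comparable timing to T1 and T2.

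No new visits or instruments are needed for the outcomes already measured at T2. The cost is slightly more analysis and reporting. The fixed-time check uses one arm only and is correspondingly less precise, and the change does nothing for the two outcomes without a T2 value beyond stating the limitation.
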